### Statistical analyses

4.8. 

Descriptive statistics will be used to evaluate demographic, clinical (obstetrical and psychological) baseline characteristics of both arms. All data will be analysed according to intention to treat analysis: the data of all randomized subjects will be analysed using the groups (treatment vs. CAU) as defined at randomization. In both conditions symptoms will be measured at regular intervals, in order to monitor treatment results over time. The treatment group and CAU group will be compared on all outcomes, which will be analysed with linear mixed models (LMM). Baseline scores will be included as covariates, time as a categorical variable, and treatment condition as a fixed effect. The intercept will be treated as a random effect. Furthermore, we will use Chi-squared tests and independent *t*-tests to compare both treatment conditions at different times (alpha level 0.05), or Fisher’s Exact test and Mann–Whitney U-test when appropriate. Effect sizes from change in symptoms between baseline and post-treatment antepartum, and post-treatment postpartum will be calculated with Cohen’s d. Safety is objectified by measuring worsening of FoC/PTSD symptoms, neonatal and obstetrical outcomes, dropout, and determining the presence of adverse events. However, our study is not powered upon these safety measures, therefore this outcome will be shown descriptively.

All analyses will be performed using SPSS version 22.0 (IBM Corp, 2013).

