**Figure 2. F0002:**
[figure not shown]
Study design.

During the clinical interview, traumatic events are explored in all women with the life events checklist (LEC-5). If appropriate, subsequently the clinician administered PTSD scale (CAPS) will be administered to diagnose PTSD (childbirth related, or not). In case of several traumatic events, the CAPS will be administered for each event separately. A pregnant woman is eligible for randomization for PTSD when a PTSD diagnosis can be obtained using the CAPS, with previous childbirth being the index trauma. PTSD with index trauma other than childbirth will be registered and analysed as co-existing psychiatric disorder. When informed consent is obtained, computer-assisted randomization will take place to allocate participants to either EMDR therapy or CAU. If the woman does not meet the criteria for PTSD after previous childbirth, but does score above cut-off on the WDEQ-A, she is eligible to be randomized for FoC (Figure 1). Measurements of (PTSD and/or FoC) symptoms take place between sessions (with childbirth being the index event of the PSS-SR questionnaire): at the start of each therapy session, or in case of CAU, measurements are done two, four and six weeks after randomization by email. Post-treatment antepartum measurement takes place at about 32–34 weeks of gestational age by a blinded assessor. If there is unblinding during the interview, another assessor will finish the interview. Final follow-up takes place two to three months after childbirth. Perinatal healthcare providers are semi-blinded: randomization results are not sent to the professionals, but if a pregnant woman would like to share information with her healthcare provider it is not prohibited.

A limitation for recruitment until 20 weeks of gestation has been chosen to ensure that there is enough time for planning an interview, arranging for therapy logistics, and for scheduling three therapy sessions before post-treatment sessions will take place around 32–34 weeks of gestation.

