### Sample size

4.7. 

The main treatment outcomes of the current study are the effectiveness of EMDR therapy for treating PTSD and FoC. In practice, this corresponds to the difference in total CAPS or WDEQ scores between the EMDR and CAU group at follow-up during pregnancy. In both cases, a significance level of 0.05 and power of 80% is used. A one-sided significance level is chosen according with our hypothesis to find a reduction in PTSD or FoC symptoms. For PTSD, expecting a large effect size of at least 0.8 (Gerger et al., 2014), this results in 21 patients needed per group. The sample size was set at 25 patients each group, calculating for 20% patient attrition. For FoC, EMDR therapy effect size is not known yet. The most comparable data is EMDR therapy for dental phobia, which showed a large effect size (Doering et al., 2013). We estimated a medium effect size of 0.5, which results in 50 patients needed per group. With 20% patient attrition, this leads to a requirement of two groups of 60 patients for FoC.

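### For repeatedly measured outcomes the stated mixed model has no treatment-by-time term, so its treatment coefficient is a visit average and not the antepartum difference the trials are sized on

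*Protocol article*

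**What the plan says.** - **Target (protocol article, 4.7 Sample size).** The main outcome is expressed as "the difference in total CAPS or WDEQ scores between the EMDR and CAU group at follow-up during pregnancy". The sizing is one-sided at 0.05 with 80% power: 21 per group for PTSD (d = 0.8) and 50 per group for fear of childbirth (FoC, d = 0.5), raised to 25 and 60 for attrition.
- **Model (4.8 Statistical analyses).** "Baseline scores will be included as covariates, time as a categorical variable, and treatment condition as a fixed effect". The intercept is random. No interaction is listed, no model contrast is tied to t1, and the visits that enter are not named.
- **Further tests (4.8).** T-tests, chi-squared tests or their non-parametric and exact counterparts are also planned "to compare both treatment conditions at different times (alpha level 0.05"). The section does not say whether these or the mixed model decide.
- **Between-session measurements (4.4 Procedure).** PTSD and/or FoC symptoms are taken "at the start of each therapy session, or in case of CAU, measurements are done two, four and six weeks after randomization by email". Section 4.8 likewise describes regular symptom measurement in both conditions.
- **Table 1 (4.5 Instruments).** CAPS: t0 and t1 only. PSS-SR: t0, between sessions, t1 and t2, in both arms. WDEQ-A: screening, between sessions in the EMDR column only, and t1 in both arms. WDEQ-B: t2 only.

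**The concern.** Without a treatment-by-time term, a model with several shared post-baseline visits estimates one common treatment effect across all of them. The sizing asks a different question: how far apart the arms are at the antepartum follow-up. The first between-session score in the EMDR arm is taken at the start of session 1, before any EMDR, so that row can carry no treatment effect. The next rows come part-way through a course of at most three sessions. Averaging over them pulls the estimate towards zero whenever the effect builds up over the sessions.

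For the FoC trial, the model-based result could then answer a weaker question than the one the 60 per group were recruited for. Separately, in both trials the t1 comparison can be made in two ways (the model, or an unadjusted test at t1) and nothing fixes which one counts.

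**Working it through.** **1. Reproduce the sizing.** For a two-sample comparison at one time point, n = 2(z₀.₉₅ + z₀.₈₀)²/d², one-sided.
- d = 0.8: 2(1.645 + 0.842)²/0.64 = 19.3, so 20. The exact t calculation gives 21 (stated: 21).
- d = 0.5: 2(1.645 + 0.842)²/0.25 = 49.5, so 50. The exact t calculation gives 51 (stated: 50).

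Two-sided versions (25 and 63 by the normal formula, 26 and 64 by t) do not match. The sizing is therefore a one-sided comparison at a single visit.

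**2. What the listed model estimates, by outcome.**

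| Outcome | Post-baseline rows | Treatment coefficient |
|---|---|---|
| CAPS | t1 only | t1 difference; no averaging |
| PSS-SR | between sessions, t1, t2; both arms | average over the visits entered |
| WDEQ-A, by Procedure and 4.8 | between sessions, t1; both arms | average over four visits |
| WDEQ-A, by Table 1 | between sessions in EMDR only; t1 in both | t1 difference |

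In the last row, each visit present in one arm only has its own time parameter, which absorbs it. Only t1 informs the treatment term: 0.50, with 80% power at 50 per group. For CAPS no interaction can exist. With one post-baseline row per woman, the random intercept also cannot be separated from residual error.

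**3. Size for WDEQ-A if both arms are measured between sessions.** Assumptions, none of them in the article: effects of 0, 1/3, 2/3 and 1 times d = 0.5 at the three between-session visits and t1; a common within-woman correlation ρ of 0.3 to 0.7; no precision gain from the baseline covariate. Analysed per arm: 60 × 0.8 = 48.

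With complete data and a random intercept, the coefficient is the simple mean of the k = 4 visit differences:
- Target = 0.5 × (0 + 1/3 + 2/3 + 1)/4 = 0.25.
- SE = √[(2/48)(1 + 3ρ)/4].
- One-sided power = Φ(0.25/SE − 1.645).

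| ρ | SE | Power |
|---|---|---|
| 0.3 | 0.141 | 55% |
| 0.5 | 0.161 | 46% |
| 0.7 | 0.180 | 40% |

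For the t1 contrast, SE = √(2/48) = 0.204 and power = Φ(0.50/0.204 − 1.645) = 79%.

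**4. PSS-SR.** Extending the same profile with a full effect at t2, the five-visit average is (0 + 1/3 + 2/3 + 1 + 1)/5 = 0.6 of the t1 effect. If the t1 effect were 0.8, the target would be 0.48. The trial is not sized on the PSS-SR.

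**5. Two routes to a t1 result.** Suppose success were claimed if either of two two-sided 0.05 tests is significant, with no true effect (bivariate normal).
- WDEQ-A, four-visit average or t1 test: the statistics correlate √[(1 + 3ρ)/4], and the error is 8.4%, 7.9% and 7.2% at ρ = 0.3, 0.5 and 0.7.
- CAPS, baseline-adjusted or unadjusted t1 test: with baseline correlation r the statistics correlate √(1 − r²), and the error is 6.4%, 7.3% and 8.3% at r = 0.3, 0.5 and 0.7.

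**The case against.** The strongest reply has four parts.

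1. **Table 1 removes most of the problem.** It gives CAPS only at t1 after baseline, and between-session WDEQ-A in the EMDR arm only. On that schedule neither sized outcome is averaged over early visits. This stands in full for CAPS. For WDEQ-A it stands only if Table 1 is the correct schedule, and the Procedure section and section 4.8 describe measurement in both arms.

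2. **The postpartum visit.** A reader might infer that t2 is pooled into the FoC primary as well. The article does not support that. WDEQ-A is not given at t2, version B is a separate postpartum form, and effect sizes to the antepartum and postpartum measurements are listed separately. Nothing says that A and B are modelled as one outcome.

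3. **A t1 comparison is already planned.** The per-time tests would supply it, and a t1 t-test matches the sizing. Some of the listed tests also clearly serve categorical outcomes or outcomes measured once. This is fair, but those tests are introduced after the mixed model as an addition, and neither is named as deciding.

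4. **The article is condensed.** An analysis plan may hold the interaction and name the visits. That is a reason for restraint, and silence alone would be no finding. Here, though, the article lists the model's terms, and the list does not produce the quantity that section 4.7 sizes.

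**Conclusion.** The point holds for outcomes measured repeatedly in both arms. It is certain for the PSS-SR, which is not a sizing outcome, and conditional for the FoC primary, WDEQ-A, on whether care-as-usual women are measured between sessions. The documents disagree on that.

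A reader might infer that both trials lose power on their primary outcome. They do not: the PTSD trial's CAPS analysis has one post-baseline visit, so its estimate is the t1 difference.

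For WDEQ-A, if both arms are measured, the model would target about 0.25 instead of 0.50, with power of about 40–55% instead of about 79%. These figures illustrate an assumed effect profile and correlation range; they are not predictions. A faster build-up of effect would dilute less. The session-1 row carries no effect under any profile.

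The unnamed deciding test affects both trials. The 6–8% error rates apply only if either significant result would be claimed as success, which the article does not state.

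**What to change.** 1. Reconcile the Procedure section with Table 1 on whether WDEQ-A is collected between sessions in the care-as-usual arm, and state which visits enter each model.
2. Add treatment-by-time to the mixed model for WDEQ-A and PSS-SR. Do not pool WDEQ-B with WDEQ-A.
3. For CAPS, use a baseline-adjusted comparison at t1. The interaction and the random intercept have no role with one post-baseline measurement.
4. Name the baseline-adjusted EMDR-minus-CAU difference at t1 as the single primary test in each trial: CAPS for PTSD, WDEQ-A for FoC.
5. Label the per-time t-tests and Mann–Whitney tests of the same outcomes as secondary or descriptive.

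Cost: wording in the analysis section and a correction to the Procedure section or Table 1. No new data and no change in sample size are needed, since the t1 contrast is what the 21 and 50 per group were computed for. The change should be made before unblinding.

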### Cost-effectiveness analysis

4.9. 

A cost-effectiveness analysis by a societal perspective will be performed, including a sensitivity analysis. All costs in maternal care during pregnancy, delivery and the first three months postpartum will be collected. This includes direct costs (e.g. visits to primary healthcare and obstetric hospital services, procedures, medication, and maternal admission), but also indirect costs (e.g. prolonged maternity leave, partner taking days off). Also, self-reported costs made by the patient will be collected (e.g. alternative medicine, antenatal courses). In addition, neonatal admission costs will be included. As far as possible, true costs will be collected besides using the Dutch system of hospital pricing that is based on diagnosis and procedure codes. Information will be derived from obstetric patient records, and the postpartum questionnaire that includes questions about healthcare use and additional costs.

## Discussion

5. 

The OptiMUM-study has several strengths resulting in a potentially innovative study. Firstly, it is a randomized controlled trial which will provide answers in a patient population where research is scarce. Secondly, the present study is a large study, comprising inclusion in university and teaching hospitals, but also in community midwifery practices. This will result in a decent cross-section of the population and including women with low, medium and high risk pregnancies. Also, PTSD and psychological comorbidity will be assessed with validated clinical interviews, which is an added value compared to many previous studies using self-report questionnaires (Rouhe et al., 2015a; Saisto et al., 2001; Toohill et al., 2014). Furthermore, besides effectiveness, obstetric and neonatal outcome is taken into account. This may be an important contribution since our study is the first controlled study with an intervention for PTSD during pregnancy instead of postpartum. Finally, cost-effectiveness analysis is added to this study. As we expect symptoms of PTSD or FoC to decrease as a result of EMDR therapy, it is likely that costs of treatment are well compensated by prevented caesarean section and fewer complications; in particular because costs of EMDR therapy are relatively low compared to costs of medical complications.

There are several limitations to be expected. Comparing EMDR with CAU is a compromise, since there is no gold standard intervention during pregnancy. Adding a waitlist-control condition was not possible, since childbirth characteristics are the outcome measures in this study. The same holds true for a placebo-intervention group due to limited financial resources at the start of this study. We estimate the influence of more patient-professional contacts (6.5 h instead of 2 h) for the EMDR group as a small confounding factor. It is also possible that patients in the CAU group will search for professional help as a result of the screening procedure for this study, which potentially could raise awareness about their PTSD symptoms or FoC. Data about all types of treatments followed by patients (in both groups) are collected. Lastly, while prevalence rates of PTSD after childbirth are known, it is however unknown how many of those women will have a subsequent pregnancy.

If EMDR therapy proves to be safe and effective during pregnancy in treating PTSD after childbirth and FoC, these are strong arguments for standard screening pregnant women for these psychological conditions, and to refer them for treatment in an early phase of pregnancy.

## Trial status

6. 

Currently screening and recruiting participants.
